### Ethics

The study was approved by the Ethics Committee of Mianyang Central Hospital (NO 2019YJ30). The ethics committee will supervise and administer the study.

### Status

This trial was registered in the ChiCTR (NO: ChiCTR1900023401). The recruitment starts in January 2021 and is planned to be completed in two years.

## Discussion

Approximately one-third of patients with advanced malignant tumors will experience bone metastasis, and the spine is the most common bone metastasis, especially the lumbar spine and thoracic [9, 10]. Patients with bone metastasis often present with severe pain that is difficult to control. Some patients with vertebral metastasis even have pathological fractures and spinal cord compression. Radiotherapy is an effective treatment for alleviating the symptoms of bone metastasis [11–13].

The 2017 ASTRO update on palliative radiotherapy for bone metastases continues to recommend that patients with bone metastases can be selectively treated with 8 Gy/1 f, 20 Gy/5 f, 2 Gy/6 f, or 30 Gy/10 f with four different fractionation methods [14–16]. The 30 Gy/10 f and 8 Gy/1 f doses are widely used in conventional radiotherapy. Existing research has shown that the effects on pain relief of single radiotherapy and fractional radiotherapy are similar [11, 15–18]. However, Rades et al. showed that the recurrence of pain caused by vertebral metastases treated with large fractionation therapy could be as high as 26%, compared with conventional long-term treatment with 30 Gy/10 f, which showed better local control [19]. This is the basis for the selection of 30 Gy/10 F fractionated irradiation in our trial. We suspect that the reason for the difference in pain control and duration of pain relief may be related to the dose limitation of spinal nerves in patients with vertebral metastases. Therefore, current research on radiotherapy of vertebral metastases focuses on increasing the radiation dose without increasing the side effects to achieve better pain control [20].

According tothe2012 ISRC consensus guidelines on the target volume of spinal SRS, unless the spinous processes, lamina / bilateral pedicle and vertebral body are affected or there are extensive metastatic diseases around the epidural space, the circumferential TVs around the spinal cord should not be used. The guidelines emphasized that published guidelines on indications and practice patterns for spinal SRS are limited and there is no consensus on the definition of target volume [2]. We propose a safe and effective reduction of the target area in IGRT radiotherapy, which can effectively avoid the excessive irradiation of nerve, spinal cord and other normal tissues, and correspondingly improve the target dose setting.

If this trial can prove that local irradiation is equivalent to whole vertebral body irradiation in terms of pain relief, then the next step will be to increase the irradiation dose on the reduced target area in order to achieve higher pain control rate of vertebral metastasis and improve the quality of life of patients with vertebral metastasis.

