**Methods:**

This study aims to verify whether reducing the radiotherapy range for vertebral metastases can achieve the same effect as whole vertebral radiotherapy while minimizing side effects. Sixty-six patients with pain caused by vertebral metastasis were randomly divided into two groups. The study group is receiving partial vertebrae body radiotherapy at the regions of abnormal signal, suspected invasion, and adjacent subclinical focus of vertebral metastasis, and the control group is receiving the same dose of radiotherapy on whole vertebrae body where metastasis occurred. After radiotherapy, along-term follow-up of patients will determine pain relief and side effects.

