### Statistical analysis and randomization

We estimated the sample size based on paper of Fleiss, JL et al. [7]. We performed non-inferiority and equivalence trials with α = 0.025, 1-β = 0.8 and non-inferiority *Δ* = -0.15 using Pearson*X*^2^test, power = 0.809, *H*0: πt—πc ≤ -0.15, *H*1: πt—πc > -0.15.We estimate a loss to follow-up rate of 10% and the resultant required number of patients was 66. The rate of pain relief in patients with vertebral metastases receiving radiotherapy will be measured according to the results of previous trials including that by Howell et al. [8]. Randomization will be administered centrally by the SPSS24.0 software at Mianyang central hospital. Patients who meet the inclusion criteria will be randomized on a1:1 basis to one of the 2 groups. The randomization will conduct by Mianyang Central Hospital through spss24.0 software. Patients who meet the enrollment conditions will enter the control group and the study group in a ratio of 1:1.

The number, proportion and 95% confidence interval of patients with pain relief will be reported. The related toxicity will analyze by Fisher exact test.

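### The design label and the Discussion speak of equivalence, but the only stated hypotheses are one-sided non-inferiority, so a positive result supports non-inferiority alone

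*Protocol article*

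**What the plan says.** Four places in the protocol article bear on the claim.

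- **Statistical analysis and randomization.** The design is introduced by "We performed non-inferiority and equivalence trials with α = 0.025, 1-β = 0.8". One margin follows (-0.15), then one pair of hypotheses on the difference πt - πc: H0 at or below -0.15, H1 above -0.15. The stated power is 0.809. On size: "We estimate a loss to follow-up rate of 10% and the resultant required number of patients was 66".
- **Discussion, closing paragraph.** The next step, a higher dose on the reduced target, is conditional: "If this trial can prove that local irradiation is equivalent to whole vertebral body irradiation in terms of pain relief".
- **Abstract, Methods.** The aim is to verify whether "reducing the radiotherapy range for vertebral metastases can achieve the same effect as whole vertebral radiotherapy while minimizing side effects".
- **Abstract, Discussion.** The expected result is pain control no worse than with whole vertebral irradiation, which is a non-inferiority statement.

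**The concern.** Non-inferiority and equivalence are different claims. Non-inferiority bounds the difference on one side. Equivalence bounds it on both, and needs two margins and two one-sided tests (or a confidence interval lying wholly between the margins). The design label names both claims, while the hypotheses cover only the first.

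If a rejection of H0 were read as equivalence, that word would rest on no test and no controlled error rate. It would also obscure what a pass allows: a true loss of relief of just under 15 points is compatible with H1. The Discussion ties the next study to the claim that the stated test does not address.

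**Working it through.** **1. What the stated test can show.** The test rejects H0 when the lower confidence limit for πt - πc lies above -0.15. The upper limit plays no part in that decision. The conclusion is a difference greater than -0.15 and nothing more. This step needs no assumption about rates.

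**2. The stated size belongs to the one-sided test.** The article gives no expected relief rates; it says only "The rate of pain relief in patients with vertebral metastases receiving radiotherapy will be measured according to the results of previous trials". The figure of 66 therefore cannot be reproduced directly, but it can be solved backwards. With equal true rates p, margin 0.15, one-sided alpha 0.025 and power 0.80:

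n per arm = (1.960 + 0.842)² × 2p(1-p) / 0.15²

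At p = 0.955: 7.849 × 0.08595 / 0.0225 = 29.98, so 30 per arm and 60 in total. Adding 10% gives 60 × 1.10 = 66. (Dividing by 0.90 gives 66.7, so 67.)

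Power with 30 per arm is Φ(0.15/SE - 1.96), with SE = √(2p(1-p)/30). At p = 0.956, SE = 0.0530 and power is about 0.81, in line with the stated 0.809. Other inputs also fit, such as 0.70 in control against 0.85 in the study arm. The equal-rate solution is thus one possible basis, not the documented one.

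**3. A pass on the stated test is not evidence of equivalence.** Take 0.70 against 0.85, a true difference of +0.15.

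- SE = √(0.70 × 0.30/30 + 0.85 × 0.15/30) = √(0.00700 + 0.00425) = 0.106.
- Non-inferiority power = Φ((0.15 + 0.15)/0.106 - 1.96) = Φ(0.87), about 0.81.

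The non-inferiority test would pass about four times in five although the arms differ by 15 points. With an upper margin of +0.15 these arms are by definition not equivalent. Two one-sided tests have power of about 0 here, as they should.

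**4. Illustration: what an equivalence test would do with these patients.** Assumptions that are not in the article: 30 evaluable per arm, equal true rates, an upper margin of +0.15 to mirror the lower one, and 0.025 for each one-sided test. Equivalence is declared when the 95% Wald interval lies inside ±0.15. Power is summed exactly over both binomial distributions.

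| Common true rate | 95% half-width, 1.96 × SE | Non-inferiority power (exact) | Equivalence power (exact) |
|---|---|---|---|
| 0.60 | 0.248 | 0.23 | 0.00 |
| 0.70 | 0.232 | 0.26 | 0.00 |
| 0.80 | 0.202 | 0.34 | 0.002 |
| 0.85 | 0.181 | 0.40 | 0.02 |
| 0.90 | 0.152 | 0.52 | 0.15 |
| 0.955 | 0.105 | 0.79 | 0.60 |

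At 0.50 equivalence power is also 0.00. The normal approximation, 2Φ(0.15/SE - 1.96) - 1, gives 0.60 at 0.955. At 0.90 the half-width barely exceeds the margin; the approximation then gives a value just below zero, so the exact 0.15 is the one to use. With 0.05 per test, exact power is 0.26 at 0.90 and 0.73 at 0.955.

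**The case against.** The case on the other side has four parts.

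- **The document promises nothing of the kind.** A reader might infer a promise to conclude equivalence. The Discussion sentence is conditional, describes a possible next step and sets no analysis rule. The Abstract's expected result is already worded as non-inferiority and matches H1. This stands, and it is why the point concerns inconsistent wording. It does not remove the inconsistency, because the design label sits in the same sentence as the one-sided margin.
- **Equivalence is not out of reach at this size.** A reader might infer that 66 patients could never show it. The article gives no relief rates and no upper margin, so no such statement follows. Near a rate of 0.955 an equivalence test would succeed about 60% of the time. This stands.
- **The power figures do not bear on the remedy.** At rates of 0.60 to 0.80 non-inferiority power is itself only about 0.23 to 0.34, so much of the shortfall comes from the unstated rates and not from the word equivalence. This stands too. The figures are illustrative and are no argument that the trial is mis-sized for equivalence.
- **The aim in the Abstract is lay phrasing.** Speaking there of the same effect is weak evidence of a statistical claim. Agreed; aligning it is desirable but secondary.

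A separate analysis plan might add a second test. This article would still carry a design label that its own hypotheses do not match.

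**Conclusion.** The point holds as a contradiction between the stated hypotheses and the wording of the claim. The hypotheses support non-inferiority within 15 percentage points and nothing beyond it; that conclusion needs no assumption. The design label in the statistics section and the next-step condition in the Discussion go further than the test, while the Abstract's expected result does not.

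The documents do not support the stronger readings, that equivalence is promised or that it is unattainable with 66 patients. Under the assumptions listed in the working, equivalence power is about 0.02 or less for rates up to 0.85, 0.15 at 0.90 and about 0.60 at 0.955. That is underpowered, but at the highest rate far from impossible.

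**What to change.** - **Statistical analysis and randomization:** delete the reference to equivalence, so that the design is called non-inferiority only.
- **Discussion, closing paragraph:** replace *is equivalent to* with *is non-inferior to (margin 15 percentage points)*. The condition for the next study then becomes the result that the trial tests.
- **Abstract, Methods (preferable, not essential):** bring the stated aim into line with the non-inferiority wording already used for the expected result.

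The hypotheses, the test and the 66 patients stay unchanged. The only cost is a more modest claim. If equivalence is really wanted, wording is not enough: the plan would need an upper margin, a second one-sided test, stated relief rates and a new sample size.

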## Data Availability

All data generated or analyzed during this study are included in this published article.

## Abbreviations

ASTRO: American Society for Therapeutic Radiology and Oncology
ISRC: International Spine Radiosurgery Consortium
3D-CRT: 3-dimensional conformal radiation therapy
CTV: Clinical target volume
SBRT: Stereotactic body radiation therapy
IMRT: Intensity-modulated radiation therapy
ChiCTR: Chinese Clinical Trial Registry
NYHA: New York Heart Association classification
IGRT: Image-guided radiation therapy
ECOG: Eastern Cooperative Oncology Group
MedDRA: Medical Dictionary for Regulatory Activities
CTCAE: Common Terminology Criteria Adverse Events
